#### Who will take informed consent?

4.1.2

In this clinical trial, the responsibility for ensuring that potential participants understand and agree to participate will be assumed by qualified and professionally trained members of the research team, which primarily includes the Principal Investigator in charge of the project and/or the Clinical Research Coordinator. These professionals have completed comprehensive training in ethical research practices, including Good Clinical Practice (GCP) certification, to ensure that they have the ability to communicate with potential participants in a clear, detailed and non-coercive manner. The informed consent process will be conducted through a series of detailed and transparent steps to ensure that each potential participant fully understands the objectives, process, possible risks and benefits of the study, as well as their rights and obligations. This process includes providing a comprehensive Participant Information Sheet (PIS) that details the study’s purpose, procedures, potential risks and benefits, confidentiality and data security measures, and the voluntary nature of participation, including contact information for the research team. Eligible patients will be given at least 48 hours to review the PIS, ask any questions, and discuss their potential participation with family, friends, or healthcare providers if they wish. This period is designed to ensure that patients do not feel rushed and can thoroughly consider all aspects of the study before providing their consent. This process involves a one-on-one meeting with the participant, during which the researcher will brief them in detail about the study and answer any questions, ensuring that each participant fully understands the study’s objectives, procedures, possible risks and benefits, and their rights and obligations. Written consent will only be collected when it is confirmed that the participant has been fully informed of all relevant information and is voluntarily agreeing to take part in the study. Patients included in this study will not have severe cognitive impairment, but for those participants with limited mobility, consent will be sought from their legal guardian or authorized agent, ensuring that the agent fully understands the research and consents on behalf of the participant. By implementing these measures, we are committed to upholding the rights of participants and ensuring that the research complies with ethical and legal standards.

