##### Inclusion criteria

4.1.1.1

- Diagnosed by cranial CT or MRI and meeting the diagnostic criteria for stroke as revised by the 4th Cerebrovascular Disease Conference.

- Meet the diagnostic criteria for depression in Chinese Classification and Diagnostic Criteria for Mental Disorders CCMD-3.

- Age 30~80 years old, gender is not limited.

- PHQ-9 score ≥5.

- No severe cognitive impairment.

- Those with no history of depression before stroke.

- Normal sense of smell.

- Informed consent and voluntary enrollment in the study.

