## Ethics statement

This study received approval from the Ethics Committee of the Second Rehabilitation Hospital of Shanghai(approval number: 2023-20-01) and was registered with the China Clinical Trial Registration Center in January 2024 (registration number: ChiCTR2400079491). All participants are required to sign a written informed consent form in accordance with the Helsinki Declaration prior to their involvement.

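### The consent section makes limited mobility, not lack of capacity or inability to sign, the trigger for proxy consent, in conflict with its own preceding sentence and with the Ethics statement

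*Protocol article*

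**What the plan says.** Section 4.1.2 (Who will take informed consent?) sets out a patient-centred process: an information sheet, at least 48 hours to consider it, and a one-on-one meeting. It then gives a general rule: "Written consent will only be collected when it is confirmed that the participant has been fully informed of all relevant information", and that the participant is taking part by free choice.

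The next sentence opens with "Patients included in this study will not have severe cognitive impairment" and continues, after the word 'but', with "for those participants with limited mobility, consent will be sought from their legal guardian or authorized agent". It describes the agent's part as "ensuring that the agent fully understands the research and consents on behalf of the participant".

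Two other places bear on the same question. The inclusion criteria (4.1.1.1) list "No severe cognitive impairment" and "Informed consent and voluntary enrollment in the study". The Ethics statement says: "All participants are required to sign a written informed consent form in accordance with the Helsinki Declaration prior to their involvement". Neither provides for an agent.

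**The concern.** The proxy route opens on a physical condition. Reduced mobility after a stroke says nothing about whether a patient can understand the trial and decide on it. The sentence mentions neither an assessment of capacity nor an inability to write. As it stands, it permits a patient who can decide to be entered on someone else's consent.

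The main stake is participant protection. One of the three arms involves daily 30-minute inhalation of burned herbal powder for four weeks (4.2.2.3), and section 1.1 says that the safety of herbal powders as incense still needs careful assessment.

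There is a smaller scientific stake. The recruitment rate is a primary feasibility outcome, judged against a threshold of 70% (4.3.1). Where an agent decides, that rate partly measures the agent's willingness instead of the patient's.

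**Working it through.** No arithmetic applies: the plan states no figure on this point, so the check is a comparison of the texts.

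1. **Trigger.** Section 4.1.2 names limited mobility. It does not define the term, and it mentions neither lack of capacity nor inability to sign.
2. **Who decides.** The agent is to understand the research and consent for the participant ("ensuring that the agent fully understands the research and consents on behalf of the participant"). That describes a decision-maker, not a witness or a scribe.
3. **To whom it applies.** The sentence first sets severe cognitive impairment aside ("Patients included in this study will not have severe cognitive impairment"), in line with the inclusion criterion "No severe cognitive impairment", and then introduces the proxy route with 'but'. It therefore reads as an exception for patients who are not severely impaired.
4. **Against the sentence before it.** The general rule allows written consent only once the participant has been informed and is willing. If the agent's consent replaces the participant's, the two sentences disagree. If it does not, the proxy sentence does not say what it adds.
5. **Against the Ethics statement.** "All participants are required to sign a written informed consent form" has no exception. Staff who accept an agent's consent in place of the patient's signature follow 4.1.2 and depart from the Ethics statement. Staff who require the patient's signature do the reverse.
6. **Against the inclusion criterion.** "Informed consent and voluntary enrollment in the study" does not say whose consent is meant. Entry on an agent's decision sits poorly with voluntary enrolment, but this is a tension, not a flat contradiction.
7. **Can such patients enter?** Yes. The exclusion criteria (4.1.1.2) remove serious bone, joint and muscle disorders but do not name motor deficit after stroke. All participants are inpatients of a rehabilitation hospital. How many have limited mobility is not stated and cannot be derived.
8. **Which outcomes are touched?** Recruitment counts eligible patients who enter (4.3.1, 8.1.1), so it depends on whoever consents. Adherence is session completion taken from participant logs (4.3.1), so it records attendance after entry and not who signed.

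**The case against.** The strongest defence is that section 4.1.2 should be read as a whole. The 48-hour period, the one-on-one meeting and the voluntary-agreement rule are written for all participants and exempt nobody with limited mobility. On that reading the agent's consent comes on top of the patient's agreement or formally records it, and staff who apply the whole section must still confirm that the patient is willing. Participants may also withdraw or stop treatment at their own request (4.1.1.3, 4.2.3), so an agent's signature does not bind a competent patient to daily sessions.

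Much of this stands. It rules out saying that competent patients would be entered against their will, or that every site would simply take the family's decision. It does not rescue the sentence. Wording under which the agent consents on the participant's behalf makes the milder reading the less natural one. Even on that reading the trigger is wrong and the Ethics statement has no matching provision.

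Three stronger readings are tempting, and the documents do not support them:

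- **A large share of the 99 planned participants is affected.** Limited mobility is undefined and no mobility figures are given. The rehabilitation content shows that therapy is delivered, not how many patients would meet the trigger.
- **Adherence is distorted as well.** Adherence is logged attendance by inpatients who may stop when they wish. Nothing links it to who gave consent.
- **The inclusion criterion is breached outright.** That criterion does not specify the participant's own consent. The firm conflicts are within 4.1.2 and with the Ethics statement.

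The condensed article format is no answer either, because the fault lies between statements that are all printed.

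**Conclusion.** The point holds as an internal inconsistency with a consequence for participant protection. Section 4.1.2 uses the wrong trigger for proxy consent. It thereby contradicts the rule immediately before it and the Ethics statement, and it fits poorly with voluntary enrolment.

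It permits, but does not require, entry of a patient able to decide on an agent's consent. For any such patient the recruitment rate may partly reflect the agent's choice. The number affected is unknown, and no effect on adherence, allocation, outcome assessment or analysis is shown.

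The conclusion rests on reading the agent's role as the words give it, and on mobility and capacity being separate matters. It does not assume that every patient without severe cognitive impairment has capacity; any doubt on that score is a reason to make capacity the test. The correction should be made because it settles who decides on entry and costs very little, not because of damage to the primary outcomes.

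**What to change.** In section 4.1.2, remove limited mobility as a reason for consent by a guardian or agent. State that every participant able to decide consents personally, whatever their mobility. Add that where a participant cannot physically sign, another person only records the participant's own decision, for example as a witness. Word the Ethics statement to allow for that form of documentation, so that it and sections 4.1.1.1 and 4.1.2 agree.

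The cost is one sentence in the consent procedure with a matching phrase in the Ethics statement, notification of the ethics committee, and a witness signature now and then. The one-on-one consent meeting is already planned, so no further visit is needed.

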
#### Additional consent provisions for collection and use of participant data and biological specimens

4.1.3

This study does not plan to collect or use participants’ data and biospecimens for any ancillary research. Therefore, participants will not be asked to provide additional consent for this purpose. All data and specimens collected will be used only for the primary research purpose of this study and in strict compliance with relevant ethical and privacy protection standards.

### Interventions

4.2

#### Explanation for the choice of comparators

4.2.1

In this study, we aim to evaluate the effectiveness of CBT and Aromatherapy Inhalation interventions in the rehabilitation of PSD. To ensure the accuracy and reliability of our results, we have meticulously chosen the following comparators:

##### Conventional rehabilitation treatment

4.2.1.1

Serving as the baseline comparison, all participants will receive standard rehabilitation treatments, including physical therapy, occupational therapy, acupuncture and medication management, to meet basic rehabilitation needs. This control group allows us to assess the additional benefits of CBT and Aromatherapy Inhalation interventions on top of standard care.

##### Cognitive behavioral therapy intervention

4.2.1.2

CBT is a psychosocial intervention that operates on altering patients’ cognitive and behavioral patterns to improve emotional states and functionality. The reason for selecting CBT as one of our comparators is its well-documented effectiveness in treating depression, including PSD. By including CBT as an intervention, we aim to evaluate its specific utility in the domain of stroke rehabilitation.

Through comparing these interventions, our study hopes to reveal the specific impacts and benefits of CBT and Aromatherapy Inhalation interventions on the rehabilitation process of patients with PSD, beyond conventional care. Moreover, the selection of comparators is based on the feasibility of interventions, patient acceptability, and the evidence base from previous research, aiming to provide empirical support for the comprehensive treatment of PSD.

#### Intervention description

4.2.2

##### Non-active control group

4.2.2.1

All participants receive routine standardized conventional rehabilitation treatment, with interventions delivered by the standardized rehabilitation therapy components of the Second Rehabilitation Hospital of Shanghai. Five times a week for a total of four weeks. This specialized program will be delivered by a team of 6 certified professionals, including 2 physical therapists (PTs), 2 occupational therapists (OTs), and 2 acupuncture physicians, ensuring a holistic approach to patient care. To further enhance the quality and consistency of the treatment, all therapists will receive standardized training prior to the research. This enhanced approach aims to deliver a holistic and standardized treatment experience, blending physical therapy (exercise therapy, balance training, and joint mobilization), occupational therapy (including homework training, hand training, and cognitive dysfunction training), acupuncture therapy, and health education.

##### CBT group

4.2.2.2

The CBT group will participate in a comprehensive rehabilitation regimen that integrates conventional treatments with Cognitive Behavioral Therapy (CBT), administered by trained psychotherapists. The inclusion of CBT aims to improve mental health and coping strategies, ensuring a comprehensive treatment protocol that addresses both the physical and psychological aspects of recovery for the control group. Participants will receive standard rehabilitation treatments in addition to CBT sessions conducted twice weekly, each lasting 30 minutes, over four weeks. The interventions include:

###### Emotional journaling

4.2.2.2.1

At the start of each session, patients will report on emotional changes experienced since their last session, detailing specific emotions, triggers, and duration.

###### Introduction to cognitive restructuring

4.2.2.2.2

Discussions will focus on identifying and challenging negative thought patterns and their impact on emotions, guiding patients towards a more positive mindset.

###### Behavioral activation strategies

4.2.2.2.3

Patients will be encouraged to engage in daily activities that generate positive emotional feedback, discussing challenges and coping strategies encountered during these activities.

###### Skill practice and application

4.2.2.2.4

Through case studies and role-playing, patients will strengthen their ability to apply CBT techniques, better equipping them to handle everyday challenges.

###### Summary and goal setting

4.2.2.2.5

Each session will conclude with a summary of the session’s content and the setting of goals and tasks for patients to complete before the next session.

##### Aromatherapy group

4.2.2.3

Aromatherapy group is based on conventional rehabilitation treatment, patients are given aromatic inhalation treatment for 4 weeks, once a day, 30 minutes each time. The aromatherapy intervention will be administered by physicians from the Traditional Chinese Medicine (TCM) Rehabilitation Department, who have received specialized training in herbal powder aromatherapy. The aromatherapy will be conducted daily for 30 minutes, and participants will need to travel to the designated area within the hospital every day for this 30-minute intervention. Since all patients are inpatients, they will simply need to coordinate the timing with the hospital schedule. Selected herbs (Farfarae Flos 6g, Lysimachia christinae Hance 6g, Mume Flos 6g, Sophora tonkinensis Gagnep 6g, Polygoni multiflori Caulis 6g, Ziziphi Spinosae Semen 6g, Liquidambar formosana Hance 12g) will be ground into fragrant powder, and the aroma will be lit for patients to inhale in a 15 m² treatment room. Ensure that the diffused aromatic odor can fully fill the space but not overpowering.

In addressing safety concerns, the study excludes individuals with respiratory conditions like asthma or allergies, to avoid any potential exacerbation of symptoms. The therapy sessions will be held in a treatment room within the hospital that is equipped with a ventilation device. This ensures effective dispersal of the aromatic smoke and maintains the indoor air quality. The ventilation device provides continuous air circulation to keep the smoke concentration at a safe level. Additionally, each therapy session will be closely monitored by medical professionals who are ready to manage any adverse reactions immediately. These measures ensure the safety of participants while adhering to the ethical standards of the research.

All interventions will be conducted at the rehabilitation hospital. Since all patients are inpatients, they will only need to coordinate with the staff to schedule and participate in the intervention sessions, ensuring convenience and consistency. All groups will receive the same patient-centered and standardized conventional treatment protocol, which is uniformly administered across all participants to ensure consistency. However, the CBT group and the aromatherapy group will receive 4 weeks of corresponding treatment in addition to the conventional treatment.

#### Criteria for discontinuing or modifying allocated interventions

4.2.3

For patients with PSD who received the aromatherapy inhalation intervention, if a serious adverse reaction (e.g., an allergic reaction) occurs during the treatment, the research team will immediately stop the treatment for that participant and carry out the necessary medical interventions. At the same time, if the participant voluntarily requests to stop the treatment, we will record his/her request and respect his/her decision. Participants’ depressive symptoms will be regularly assessed in the study and adjustments to the treatment regimen will be considered if significant improvement or worsening is observed. All these adjustments will be made under the guidance of the research ethics committee to ensure that the safety and rights of the participants are protected.

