**Methods:**

This single-blind pilot randomized controlled trial will be conducted at the Second Rehabilitation Hospital of Shanghai, enrolling ninety-nine post-stroke patients with PSD. Participants will be randomized into three groups: a Non-Active Control Group receiving standardized rehabilitation therapy, a CBT Group receiving conventional rehabilitation with bi-weekly CBT sessions, and an Aromatherapy Group receiving conventional rehabilitation with daily aromatic inhalation sessions. Interventions will last for four weeks, with efficacy assessed at baseline, post-intervention, and one month post-intervention. Rating scales will be used to measure changes in depression, sleep quality, cognitive function, and quality of life. EEG and fNIRS will specifically be used to measure changes in cerebral cortex activity and their correlations with depression. Feasibility will be evaluated through recruitment, intervention adherence, assessment completion and safety assessment.

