## Trial design

3

A single-blind, pilot randomized controlled trial will be conducted to evaluate the preliminary efficacy and feasibility of mixed herb aromatherapy compared to standard care and CBT. This study will enroll ninety-nine post-stroke patients with PSD at the Second Rehabilitation Hospital of Shanghai. Prior to initiating rehabilitation, demographic details of all participants, including name, gender, age, education level, and medical history, will be collected. A centralized, web-based service provided by Research Randomizer (https://www.randomizer.org/) will be utilized to generate a randomization sequence, ensuring an even distribution of patients between the three groups: the non-active control group (receiving standard care), the aromatherapy group (undergoing daily aromatherapy inhalation), and the CBT group (receiving CBT sessions twice weekly) in a 1:1:1 ratio. The intervention will last for four weeks.

Primary feasibility outcomes will include recruitment rates, adherence to the intervention and completion rates. Recruitment rates will be monitored and documented weekly. Adherence will be tracked through participant logs, ensuring that each session is recorded. Completion rates will be calculated at the study’s conclusion.

Evaluation of intervention effectiveness will be conducted at three time points: before the intervention (baseline), immediately after the intervention (four weeks), and one month post-intervention, to assess the effectiveness of the treatments (see **Figure 1** for details).

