#### Secondary outcome measures

4.3.2

Patient Health Questionnaire-9 (PHQ-9): The Chinese version of PHQ-9 has been translated and validated, demonstrating good validity and reliability for assessing depression severity among Chinese populations (42). It consists of nine items representing various aspects of depressive symptoms with high reliability and easy to understand. Each item is rated on a four-point scale, with the patient choosing the most compatible answer based on how they felt over a two-week period. 0: no problem at all; 1: a few days; 2: most of the time; 3: every day. The total score ranges from 0 to 27, with higher scores indicating more severe depressive symptoms. Score 0 to 4: no or minimal depressive symptoms; 5 to 9: mild depression; 10 to 14: moderate depression; 15 to 19: moderately severe depression; 20 to 27: severe depression.Hospital Anxiety and Depression Scale: We will use the translated and validated Chinese version of the HADS. This version has demonstrated good validity and reliability in studies involving Chinese populations (43). The self-report scale is widely used to assess patients’ levels of anxiety and depression in healthcare settings. The scale was developed by Zigmond and Snaith in 1983 and is primarily designed to be used as a quick and easy measure of a patient’s psychological state under the guidance of a non-psychological professional (44). The HADS consists of 14 items, of which 7 items are used to assess depression (Items #2, 4, 6, 8, 10, 12, and 14 items) and 7 items of the scale are used to assess anxiety (Items #1, 3, 5, 7, 9, 11, and 13). Each item has a 4-point scale, with each item scored on a scale ranging from 0 to 3, and the total score ranging from 0 to 21.Mini-Mental State Examination (MMSE): We will use the translated and validated Chinese version of the MMSE. This version has been widely applied in various studies and has proven effective and reliable for assessing cognitive function in Chinese populations (45). The MMSE is a simple instrument widely used for the assessment of cognitive functioning and consists of 30 items with a total score of 30 points. It includes attention and calculation ability (5 points), memory (3 points), orientation (10 points), language (8 points), and executive function (4 points). 0-9: moderate cognitive disorder; 10-17: mild cognitive disorder; 18-23: mild cognitive impairment; and 24-30: normal cognitive level.Pittsburgh sleep quality index (PSQI): We will use the Chinese translated version of the PSQI. The translated version has been validated and shown to be effective and reliable in assessing sleep quality among Chinese populations (46). The main purpose of the PSQI is to comprehensively assess the quality of an individual’s sleep, including sleep duration, difficulty falling asleep, sleep effect, sleep depth, number of sleep awakenings, and sleep medication use (47). It contains 7 main subscales that assess different aspects of sleep: subjective sleep quality, difficulty falling asleep, sleep duration, sleep effect, sleep depth, use of medications, and daytime dysfunction. Each subscale has a score range of 0-3 and a total score of 21, with higher scores representing poorer sleep quality. a total PSQI score of >5 is usually considered poor sleep quality.Stroke Specific Quality of Life Scale (SS-QOL): We will use the translated and validated Chinese version of the SS-QOL. This version has demonstrated good validity and reliability for assessing the quality of life in Chinese stroke patients (48). The scale includes 12 dimensions of energy, family role, language, activity, mood, personality, self-care, social role, thinking, upper limb function, vision, and work/productivity, with each entry on a 5-point scale (1 to 5). The total score ranged from 49 to 245, with higher scores indicating better quality of life.A 32-channel wireless multichannel EEG acquisition and analysis system from Xi’an ZhenTec Intelligence Technology, ZhenTec NT1, will be used for brain EEG data acquisition. Saline electrodes will be used and placed according to the international standard lead 10-20 electrode system position. The sampling rate will be 1000 Hz and electrode impedance will be kept below 10 kΩ. Resting state EEG will be recorded from the patients before and after four weeks of intervention. Resting-state EEG: EEG data will be recorded for 5 minutes in a quiet state. LZC complexity nonlinear feature extraction will be performed for the full frequency band (0.6-46Hz), δ (1-3.5Hz), θ (4-7Hz), α (8-13Hz), and β (13-30Hz) frequency bands of the resting-state EEG, respectively, to calculate the LZC values.A 64-channel fNIRS device (BS-2000L, Wuhan Znion Technology Co., Ltd., China) will be used to collect information on changes in oxygenated hemoglobin (HbO) and deoxyhemoglobin (HbR) concentrations in the prefrontal lobe and part of the temporal lobe of the subjects during the VFT task. The VFT consists of the following components: (1)A 30-second pre-task baseline period to establish a resting state, during which participants will be asked to repeat the sequence “12345” to ensure consistent starting conditions. (2)A 60-second task period divided into three 20-second segments, during which participants are asked to generate as many words as possible starting with given syllables (e.g., “ba,” “da,” “pa”). (3)A 70-second post-task baseline period during which participants will again repeat the sequence “12345” until the end of the assessment at 170 seconds. This task evaluates regional brain activity and forebrain functional network connectivity. Data preprocessing includes artifact removal and baseline correction using the moving average method. HbO and HbR integral values will be calculated by averaging data from all channels, representing the hemodynamic response during the task period.

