### Sequence generation

5.1

Participants will be randomized in a 1:1:1 ratio to control group, CBT group or aromatherapy group. Due to the unique characteristics of each intervention, complete blinding of participants and therapists is not possible. However, measures will be taken to minimize bias, including withholding specific hypotheses about the interventions from participants. Data collection will be performed by investigators blinded to group assignments. Furthermore, data analysis will occur under blinded conditions, with assignments coded and concealed until the conclusion of the analysis.

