### Plans to promote participant retention and complete follow-up

7.2

The follow-up of this study is scheduled 4 weeks after the end of the intervention. Regular contact will be maintained with participants by phone, email, or text message to provide study progress updates, answer participant questions, and remind of upcoming follow-up visits.

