#### Secondary outcome analysis: clinical measures

8.1.2

- Measures such as PHQ-9, HADS, MMSE, PSQI, and SS-QOL will be summarized at each time point using descriptive statistics to observe potential effects and trends. Given the limited sample size, inferential analysis will be avoided. Instead, the focus will be on descriptive statistics and comparison with minimal important changes (MIC) to assess the clinical relevance of observed changes.

- To compare the efficacy of aromatherapy versus CBT, non-inferiority tests will be conducted to determine if the efficacy of aromatherapy is not significantly worse than that of CBT. The non-inferiority margin will be defined *a priori*, typically set at a 10% margin, indicating that aromatherapy is considered non-inferior if the difference in improvement between CBT and aromatherapy falls within this margin. If assumptions for parametric tests are violated, descriptive statistics will be used to summarize the data. This analysis will highlight the potential of aromatherapy as an effective complementary therapy.

- EEG data will be processed using a bandpass filter (0.6-46 Hz) and artifacts will be removed using Independent Component Analysis (ICA). A minimum of 4 minutes of artifact-free data will be selected for further analysis. The Lempel-Ziv Complexity (LZC) values for the full frequency band (0.6-46 Hz) and specific bands: δ (1-3.5 Hz), θ (4-7 Hz), α (8-13 Hz), and β (13-30 Hz) will be summarized at baseline, post-intervention, and follow-up within each group. Changes in LZC values over time and between groups will be explored descriptively, and the relationship between changes in LZC values and improvements in PHQ-9 scores will be examined using Pearson correlation to identify potential correlations between EEG biomarkers and clinical measures of depression. This analysis will help to understand if EEG changes can be predictive of or associated with improvements in depressive symptoms, providing preliminary insights into the neurological impacts of the interventions.

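### Treatment may be adjusted on improvement or worsening of depression, but the visible text schedules no depression score during the four treatment weeks, and observation in that period differs by arm

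*Protocol article*

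**What the plan says.** Section 4.2.3, on discontinuing or modifying allocated interventions, states that "depressive symptoms will be regularly assessed in the study and adjustments to the treatment regimen will be considered". The condition attached to this is "if significant improvement or worsening is observed". It places such adjustments under the guidance of the ethics committee. It names no instrument, interval or size of change.

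The visible schedule is the same wherever it appears. The abstract has "with efficacy assessed at baseline, post-intervention, and one month post-intervention". Section 3 lists "before the intervention (baseline), immediately after the intervention (four weeks), and one month post-intervention" as the points for evaluating effectiveness. Section 7.2 adds: "The follow-up of this study is scheduled 4 weeks after the end of the intervention". Section 8.1.2 says that "PHQ-9, HADS, MMSE, PSQI, and SS-QOL will be summarized at each time point using descriptive statistics". The timeline itself is Table 1 (Section 4.4), which is not shown.

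On blinding, Section 5.1 says that "complete blinding of participants and therapists is not possible". Outcome assessors and analysts are to be blinded (Section 6.1).

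**The concern.** There are two issues in one sentence of Section 4.2.3.

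The first concerns worsening. The plan names it as a reason to consider changing treatment, yet the visible text gives it no scored measurement while the allocated treatment is running. The trigger then depends on who happens to see the patient and what they ask, and that is not the same in the three arms. Worsening, and any treatment change that follows, could be detected at different rates by arm.

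The second concerns improvement. Changing allocated treatment because a patient is doing well, in an open-treatment trial, makes the treatment received depend on the outcome that is later compared. Section 8.1.2 plans a non-inferiority comparison of aromatherapy with CBT. If improvers in one arm had their regimen altered before week 4, the week-4 difference would no longer describe the two regimens as allocated.

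**Working it through.** **Scheduled scores.** Two depression scales (PHQ-9 and HADS) at three time points (week 0, week 4, about week 8) give 2 × 3 = 6 scores per participant. The number strictly between week 0 and week 4 is 0, in every arm, on the visible text.

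**Allocated sessions remaining when a score becomes available** (session frequencies from Section 4.2.2):

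| Component | Sessions in 4 weeks | Left at the week-4 score | Left at a week-2 score |
|---|---|---|---|
| Aromatherapy, daily | 7 × 4 = 28 | 0 | 14 |
| CBT, twice weekly | 2 × 4 = 8 | 0 | 4 |
| Conventional, five times weekly | 5 × 4 = 20 | 0 | 10 |

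The week-4 score comes after the last allocated session, whereas a week-2 score leaves half of them. These counts cover only the allocated four-week sessions, not all inpatient care.

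**What the text provides between week 0 and week 4, side by side:**

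- All arms: contact with the rehabilitation team five times a week (Section 4.2.2.1); reports of discomfort or adverse reactions, and vital signs before and after each session (Section 4.3.1); clinicians monitoring risk (Section 9.3). None of this is tied to a depression measure.
- CBT arm: in addition, patients report emotional changes at the start of each session (Section 4.2.2.2.1). At two sessions a week this is 8 unscored reports, collected as therapy content.
- Aromatherapy arm: in addition, a trained physician accompanies the sessions (Section 5.3), up to 28 occasions.
- Control arm: neither addition.

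So the common layer is the same in all arms and the additional layer is not.

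**Size of the remedy.** The plan's recruitment figure reproduces as 30 × 1.10 = 33 per group and 3 × 33 = 99 in total. It matters here only for cost. PHQ-9 forms now: 3 × 99 = 297. With a week-2 form: 4 × 99 = 396. The increase is at most 99 forms, 33 per arm.

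**Why week 2.** The PHQ-9 is completed "with the patient choosing the most compatible answer based on how they felt over a two-week period", so a week-2 form covers the treatment received so far and nothing before it.

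**The case against.** The strongest reply is that nothing in the visible text contradicts itself. The three time points are presented as evaluations of effectiveness, whereas Section 4.2.3 concerns clinical management and does not name an outcome scale. Regular clinical assessment of inpatients is compatible with three outcome visits. Table 1 is not shown and may list an interim check. Instrument, interval and threshold are also details that a condensed article may leave to the full protocol.

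Much of this stands, and it rules out three stronger readings that a reader might take from the sentence:

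- *That the protocol contradicts itself, or that worsening would go unnoticed.* Not supported. The effectiveness visits do not exclude observation in between, CBT patients report emotional changes at every session, and Table 1 cannot be checked. The count of three time points in Section 3 makes an interim score less likely but does not exclude it.
- *That no treatment is left to adjust once the week-4 score arrives.* Not supported. Section 4.2.3 speaks of the regimen, standard care includes medication management (Section 4.2.1.1), and nothing says that inpatient care ends at week 4.
- *That the missing threshold is a defect in its own right.* Not supported, because an article may omit it.

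A further fair point is that sending a mid-treatment score to a treating clinician in an open trial may itself prompt co-intervention. That is a genuine cost of the remedy.

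What the reply does not answer is the uneven observation across arms, since no section links the common contact to mood. Nor does it answer the improvement trigger, which is in the text whatever Table 1 shows. Ethics committee guidance is a safeguard for participants but does not stop the change from depending on the outcome.

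**Conclusion.** The point holds as a cheap improvement, in two parts of different strength.

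The improvement trigger is a weakness on the text alone. It permits outcome-dependent changes to allocated treatment before week 4, with participants and therapists unblinded. How often it would be used, and in which direction it would move the comparison, cannot be judged from the document.

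The worsening trigger has no equal, scored measurement across arms during treatment: 0 of 6 scheduled scores on the visible text. This part assumes that Table 1 contains no interim depression score and that no fuller protocol supplies one. Confidence is therefore medium. The document gives no basis for estimating how many patients would worsen or be missed.

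**What to change.** 1. In Section 4.2.3, delete improvement as a reason for changing allocated treatment. This needs no new data.
2. Unless Table 1 already has such a check, add one PHQ-9 at week 2 in all three arms, for safety only. It should be read the same day by a treating clinician who is not an outcome assessor, so that assessor blinding is kept. State in Section 4.2.3 a worsening threshold in PHQ-9 points from baseline, with the value set by the sponsor. The care that follows is for the clinicians to decide.
3. State that the week-2 form does not count towards the 85% assessment-completion criterion (Sections 4.3.1 and 4.5), so that criterion is unchanged.
4. Record by arm every treatment change that follows a week-2 score, so that any co-intervention can be seen when the arms are compared.

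The cost is at most 99 short forms, clinician reading time, and one amendment through the steering committee, research department and ethics committee (Section 9.5). If the sponsor prefers not to add the form, the least change is to make the improvement deletion and reword the sentence to say that worsening is identified through routine inpatient care. That needs the same approvals but no forms, and leaves the uneven observation across arms in place.
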